## Abstract

**Background:**

Pap screening, an effective method for cervical cancer prevention, is now supported by molecular human papillomavirus (HPV) testing. Recently commercialised preventive vaccines also provide new tools for the primary prevention of cervical cancer. To determine appropriate prevention strategies, the Health General Direction, Lombardy Region, funded a project that aims to characterize and monitor HPV infections and related cervical diseases in high-risk women.

**Methods/design:**

VALHIDATE is a 5-year multicentre open prospective cohort study. It will recruit 7000 consenting women aged 13–65 years to provide information about the local biomolecular epidemiology of HPV infection and cervical diseases in high-risk women recruited from nine clinical centres and one faith-based organisation. The study will estimate the overall and type-specific prevalence of HPV infection and cervical abnormalities. It also aims to compare standard Pap screening with biomolecular screening, and to assist in the design of targeted regional prevention programs directed specifically at high-risk groups. Three groups of high-risk women: 1000 HIV-infected women (aged 26–65 years), 1000 recent migrant women (aged 26–65 years) and 3000 young women (aged 13–26 years) and 1 control group: 2000 women (aged 26–45 years) attending a spontaneous screening program, will be recruited. Sample sizes will be revised after the first year. Adult participants will undergo conventional cervical cytology, HPV DNA screening and genotyping. Paediatric participants will undergo HPV DNA testing and genotyping of urine samples. HPV DNA, cytological abnormalities and HPV types will be analysed according to demographic, epidemiological, behavioural, and clinical data collected in an electronic case report form. Overall and stratified prevalences will be estimated to analyse the associations between HPV infection and selected characteristics. Logistic regression models will be used to estimate crude and adjusted odds ratios. Cox proportional hazard models will be used to estimate hazard ratios over time and between groups.

**Discussion/main expected results:**

This study will provide substantial insight into HPV infections and related cervical diseases in high-risk groups and will help determine appropriate regional cervical cancer prevention strategies.

## Background

Cervical cancer screening with cervical cytology is a proven and effective secondary prevention strategy that can achieve a significant reduction in cervical cancer incidence in the industrialized world [1-3]. However, its efficacy is linked to the extent to which the target population is reached. Therefore, cervical cancer continues to be a major problem in the low- and medium-resourced countries of sub-Saharan Africa, South and South East Asia and Latin America [2,4-7]. Up to 70% of the estimated annual global burden of new cases and cervical cancer deaths occur in these countries because of their lack of an effective screening program [8]. Recently developed secondary prevention strategies show promise for scaling up prevention services in both developing countries and the industrialized world. These strategies are based on human papillomavirus (HPV) testing for high-risk HPV types, which are a necessary intermediate step for the development of cervical cancer and its precursors. The sole use of HPV DNA testing as a primary screening method has proven to be effective in randomized clinical trials conducted in industrialized countries as well as in simulation models [9-14]. Because the HPV DNA test also has a higher sensitivity and negative predictive value for grade II or higher cervical intraepithelial neoplasia (CIN) in immunocompetent women than conventional or liquid-based cytology, the extension of screening intervals to once every 3–5 years can be considered safe [15-17]. HPV testing is actually the recommended follow-up of abnormal cytology in women older than 30 years and after CIN treatment [18-20].

Recently commercialized cervical cancer vaccines, moreover, provide new tools for the primary prevention of cervical cancer with a very high rate of protection for more than eight years when used in women previously uninfected by the genotypes included in the vaccines [21-30]. The association of HPV-based screening and vaccination in the prevention of cervical cancer has been proven in randomized clinical trials, but several questions remain about the cost-effectiveness of the vaccine after sexual debut, the impact of non-vaccine HPV types and the best implementation practices [29,30]. The Italian Government (Ministry of Health) initiated a free vaccination program for 12-year-old adolescent girls on January 1, 2008. All Italian regions started the vaccination program during 2008 with the aim of reaching 95% vaccination coverage of the target group in 5 years (defined in “Intesa Stato-Regioni”, December 20th, 2007). In some regions, the free vaccine was also offered to other age groups. In Lombardy, the regional vaccination program began in September 2008 and offers free HPV vaccination to all 12-year olds girls. An extension to other age groups will be considered after an evaluation of the local burden and type of HPV infection among several risk groups and an analysis of the best overall strategy for the control of cervical cancer.

To determine appropriate strategies for cervical cancer prevention and to optimize the allocation of resources, the Health General Direction, Lombardy Region, funded a project that aims to characterize and monitor HPV infections and related cervical diseases in high-risk women across a wide range of ages.

## Methods/design

VALHIDATE (eVALuation and monitoring of HPV Infections and cervical relATEd Diseases in high-risk women) is a multicentre open cross-sectional and prospective cohort study conducted over a 5-year period (Dec. 2010–Dec. 2015) in the Lombardy Region. It aims to provide information about the local epidemiology of HPV infections and related cervical diseases as well as the distribution of HPV genotypes across ages and in high-risk groups of women.

The study was commissioned and funded by the Health General Direction of the Lombardy Region and has been approved by the ethical committees of the hospitals involved in the research. Approval for the storage of residual biological samples for further analysis was also obtained from the hospitals’ ethical committees.

The study will recruit 7000 consenting women aged 13–65 years through nine clinical centres in four general hospitals (4 gynaecology units, 3 infectious disease units, 2 paediatric units) and one faith-based voluntary organization that offers primary health care for migrants lacking health insurance.

One university virology laboratory, four microbiology laboratories and four pathology laboratories located in the hospitals will analyse the samples collected from the enrolled women.

The cross-sectional study was designed to estimate the prevalence of HPV infection, cervical abnormalities and HPV type-specific prevalence across a wide range of age and risk groups. The prospective cohort study was designed to compare the standard screening procedure (Pap test) with biomolecular HPV-testing across different age and risk groups and to assist in the design of targeted regional prevention programs directed specifically at high-risk groups.

The secondary objectives of the study are to: a) identify the geographical distributions of HPV 16 and HPV 18 variants and their association with clinical aspects; b) identify the prevalence, distribution and incidence of potential HPV 16 and HPV 18 vaccine escape mutants; c) monitor the HPV type distribution over time for an early identification of the type replacement phenomenon following the beginning of the vaccination campaign for 12-year-old girls in the Lombardy Region (September 2008).

### Informed consent

Written informed consent for participation in the study and for the conservation of the collected samples in a bio-bank will be asked from all eligible women and will be essential for participation in the study.

### Study population

#### *Control arm*

Two thousand women aged 26–45 years will be recruited from those attending a spontaneous Pap screening program (SPSW).

#### *Testing arms*

One thousand HIV-infected women (HIVW) will be recruited from those followed up for HIV infection in three infectious disease units. One thousand recent migrant women (less than 1 year) (RMW) will be recruited mostly through a faith-based organization, and 3000 young women (aged 13–26 years) will be recruited from those asking for a Gynaecologic (1326G) or Paediatric consultation (1318P). Those vaccinated with anti-HPV vaccines prior to enrolment or during the follow-up period will not be excluded from the study. Instead, the vaccinated participants will be considered a subgroup to be monitored and evaluated over time.

#### *Exclusion criteria*

Those with a history of histologically proven grade II or higher CIN requiring treatment, who were pregnant at the time of enrolment or who were unable to provide informed consent are excluded from the study. For participants aged < 18 years, written informed consent will be required from their parents or legal guardian.

#### *Recruitment and follow-up periods*

Participants will be recruited for 12 months; this will be extended if necessary. They will be followed up for 3 years, and the study is scheduled for completion 3 years after the last enrolment.

### Baseline evaluation and follow-up

Adult participants will undergo a medical assessment appropriate to their group (gynaecologic evaluation, and infectious disease evaluation for HIV-infected participants), cytological screening following the Italian Guidelines [31] for Cervical Cancer or algorithms modified for HIV-infected women, and HPV DNA testing. Colposcopy referral will be driven by cytology results. The conventional Pap smears will be evaluated according to the 2001 Bethesda System by four pathology laboratories.

HPV-DNA testing will be performed by the reference virology laboratory. HPV DNA-positive samples will be genotyped using a commercial kit in the four microbiology laboratories. Oncogenic risk associated with HPV types will be defined according to the 2011 IARC classification [32]. Samples with a positive HPV DNA test but with genotypes not included in the InnoLipa panel will be typed by the restriction fragments length polymorphism (RFLP) technique in the reference virology laboratory. In this reference laboratory, HPV 16- and HPV 18-positive cervical brushes or urine samples will be further subjected to a phylogenetic analysis to study the circulation of variants belonging to different geographical clusters (European and non-European).

An additional analysis for the characterization of HPV 16 and HPV 18 variants that could potentially elude the immune response induced by the vaccination (escape mutants) will be performed.

Participants with discordant results (HPV-positive/cytology-negative) will be recalled after 12 months for reassessment with cytology and HPV testing.

Paediatric participants will undergo a paediatric evaluation and HPV DNA testing of urine samples. The algorithms for the follow-up of adult and paediatric participants are presented in Figure 1, Figure 2, Figure 3, and Figure 4. All data collected during the visits and derived from cytology and biomolecular evaluations will be recorded on a specially developed secure electronic case report form (eCRF).

**Figure 1 F1:**
[figure not shown]
**Algorithm for the screening and follow-up of SPSW and RMW.** SPSW: women aged 26–65 years attending a gynaecologic visit for spontaneous screening. RMW: recently migrated women aged 26–65 years asking for medical assessment of any health problem. HPV testing: Nucleic acid extraction from cervical samples (by NucliSENS*®* EasyMAG™, bioMérieux bv, France) followed by PCR amplification of a 450-base pair fragment of ORF L1 using the degenerate primer pair ELSI-f and ELSI-r.

**Figure 2 F2:**
[figure not shown]
**Algorithm for the screening and follow-up of HIVW.** HIVW: HIV-infected women aged 26–65 years. HPV testing: Nucleic acid extraction from cervical samples (by NucliSENS*®* EasyMAG™, bioMérieux bv, France) followed by PCR amplification of a 450-base pair fragment of ORF L1 using the degenerate primer pair ELSI-f and ELSI-r.

**Figure 3 F3:**
[figure not shown]
**Algorithm for the screening and follow-up of 1326G.** 1326G: young women aged 13–26 years asking for a gynaecologic assessment. HPV testing: Nucleic acid extraction from cervical samples (by NucliSENS*®* EasyMAG™, bioMérieux bv, France) followed by PCR amplification of a 450-base pair fragment of ORF L1 using the degenerate primer pair ELSI-f and ELSI-r.

**Figure 4 F4:**
[figure not shown]
**Algorithm for the screening and follow-up of 1318P.** 1318P: young girls aged 13–18 years asking for a paediatric assessment of any health problem. HPV testing: Nucleic acid extraction from cervical samples (by NucliSENS*®* EasyMAG™, bioMérieux bv, France) followed by PCR amplification of a 450-base pair fragment of ORF L1 using the degenerate primer pair ELSI-f and ELSI-r.

### Conventional pap smears

The Pap smear sample will be obtained by using a brush (Cytobrush Plus Medscand® Medical AB, Sweden). Cervical specimens for conventional cytology will be processed by spreading the cells onto a glass slide, fixing cells within a few minutes, and then sending them to the reference pathology laboratory for investigation.

### Sample collection for molecular tests

The same cervical brush used for cytology will be then immersed and rinsed in a vial filled with 20 ml of PreservCyt® solution (ThinPrep Pap Test, Hologic Italia Srl), and stored at room temperature (RT) until processing. Ten millilitres of each PreservCyt solution containing cervical cells will be centrifuged at 3800 × g for 15 min at RT. After centrifugation, the pellet will be resuspended in 1 ml of phosphate buffered saline (PBS), transferred into a new 1.5 ml collection test tube and stored at −20 °C until nucleic acid isolation.

First-void urine samples will be collected in sterile containers, kept at RT and processed within 6–8 hours of collection. At least 15 ml of each urine sample will be centrifuged at 3800 × g for 20 min at RT. After centrifugation, the opaque phase will be recovered, transferred into a new 1.5 ml collection test tube and then centrifuged at 16,000 × g for 15 min at RT. The pellets obtained will be resuspended in 700 μl of PBS and stored at −20 °C until nucleic acid isolation.

### Colposcopy

Referral for colposcopy will be driven by the Pap results. Cytology showing atypical squamous cells or worse will be referred for colposcopy evaluation and biopsies will be taken from suspicious areas of the cervix, according to the standard procedures in Italy [33]. Biopsy results will be reported as normal, CIN grade I, II, III, or as invasive cancer, according to the international criteria [34].

### Nucleic acid extraction and HPV DNA detection

DNA will be extracted from cervical and urine samples using an automated system for total nucleic acid extraction (NucliSENS*®* EasyMAG™, bioMérieux bv, France) according to the manufacturer’s instructions. The concentration and purity of the extracted DNA will be evaluated through a Thermo Scientific NanoDrop 2000 spectrophotometer (Thermo Fisher Scientific Inc., France). DNA integrity will be assessed by amplification of a 268-base pair (bp) fragment in the ubiquitous β-globin gene using the primer pair PCO_4_ (5′–CAACTTCATCCACgTTCACC–3′) and GH_20_ (5′–gAAgAgCCAAggACAggTAC–3c′) [35].

HPV DNA will be detected by PCR amplification of a 450-bp segment of ORF L1 using the degenerate primer pair ELSI-f (5′–gCNCARggHCATAAYAATgg–3′) and ELSI-r (5′–CgNCCHAADggAAAYTgATC–3′)[36]. An equimolar mixture of each primer will be added to the PCR master mix to a final concentration of 30 pmol. PCR will be performed using GoTaq® DNA Polymerase (Promega, Madison WI, USA) according to the manufacturer’s instructions. The ELSI-f and ELSI-r primers will be used with the following amplification reaction conditions: 5 min denaturation at 94 °C followed by 40 cycles of amplification. Each cycle will consist of a denaturation step at 94 °C for 30 sec, an annealing step at 55 °C for 30 sec and an elongation step at 72 °C for 30 sec. The last cycle will be followed by a 7 min elongation step at 72 °C. Each PCR run will include positive controls (DNA extracted from HPV 16-positive cells, Caski) and negative (water) control samples. The amplification products will be revealed using an electrophoresis analysis of 2% agarose gels containing ethidium bromide. Amplified product bands will be compared with molecular weight standards (DNA Molecular Weight, Marker 100, Sigma, St. Louis, MO).

### HPV genotyping

The 450-bp fragments will be genotyped using INNO-LiPA HPV Genotyping *Extra* (Innogenetics N.V., Belgium), a line probe assay based on the principle of reverse hybridization. Part of the L1 region of the HPV genome will be amplified using SPF10 primers. The resulting biotinylated amplicons will be subjected to denaturation and hybridization with sequence-specific DNA probes for the identification of 28 different HPV genotypes: 6, 11, 16, 18, 26, 31, 33, 35, 39, 40, 43, 44, 45, 51, 52, 53, 54, 56, 58, 59, 66, 68, 69, 70, 71, 73, 74, and 82. To establish the genotype/s present in the sample, the line patterns will be compared with the interpretation chart supplied with the assay.

### HPV X

Samples for which the obtained line pattern cannot be assigned to any genotype pattern or that have no type-specific lines, but at least one positive HPV control line will be scored as HPV-positive, but untypeable (HPV X). These samples will be referred to the reference virology laboratory for genotype analysis by RFLP. The 450-bp fragments obtained by the ELSI-PCR protocol will be tested by the RFLP technique with RsaI, DdeI and HaeIII digestion enzymes (New England Biolabs, Ipswich, MA). Briefly, 10 μl of the amplified products will be added to three final mixtures of 15 μl containing 1U of each enzyme in a specific buffer. The restriction reaction will be performed at 37 °C for 1 hour and the enzymes will be then inactivated at 80 °C for 20 minutes. Fragments of different lengths will be separated on 3% agarose gel. The pattern of fragments generated by the restriction enzymes will allow for identification of all types in the genus *alpha* of Papillomaviruses.

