### Statistical analyses

#### *Cross-sectional study*

Overall and HPV type-specific prevalence will be estimated with 95% confidence intervals (CI), according to the Poisson approximation, in the four participant groups (three high-risk groups and control group). Logistic regression models will be used to estimates odds ratios (OR) and their corresponding 95% CI to quantify the associations between HPV infection and major demographic, clinical and behavioural characteristics in the four participant groups. All variables will be analysed in both univariate and multivariate models to control for major confounding factors.

Sensitivity, specificity, and positive and negative predictive values of the HPV test compared with the Pap test will be estimated overall and by group. Test performance in matched pairs will be estimated with McNemar’s tests, and proportions will be compared using Fisher’s exact tests. Exact methods will be applied when expected cell frequencies are less than five.

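### Types outside the 28-type panel are sought only when no panel type can be assigned, so their recorded prevalence is too low, and unequally so across groups and over time

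*Protocol article*

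**What the plan says.** Genotyping in the protocol article is sequential.

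- **HPV genotyping.** HPV-positive samples go to a line probe assay based on "hybridization with sequence-specific DNA probes for the identification of 28 different HPV genotypes".
- **HPV X.** RFLP is reserved for "Samples for which the obtained line pattern cannot be assigned to any genotype pattern or that have no type-specific lines", provided at least one HPV control line is positive. Of this subset the section says: "These samples will be referred to the reference virology laboratory for genotype analysis by RFLP". It gives RFLP a wider reach than the panel: "The pattern of fragments generated by the restriction enzymes will allow for identification of all types in the genus" *alpha*.
- **Baseline evaluation and follow-up.** The rule is put more loosely here: "Samples with a positive HPV DNA test but with genotypes not included in the InnoLipa panel will be typed by" RFLP. No other way of recognising such samples is given.

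Two parts of the plan use the resulting types.

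- **Statistical analyses, Cross-sectional study.** The estimates are specified as follows: "Overall and HPV type-specific prevalence will be estimated with 95% confidence intervals (CI), according to the Poisson approximation, in the four participant groups". Panel types and RFLP-identified types are not separated.
- **Methods/design, secondary objective (c)** is to "monitor the HPV type distribution over time for an early identification of the type replacement phenomenon" after vaccination of 12-year-old girls began.

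The Prospective study section leaves uncharacterised HPV X out of the definition of single and multiple infection. That rule does not deal with a non-panel type present alongside a panel type.

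**The concern.** Whether a non-panel type is recorded depends on what else is in the sample. A woman with HPV 16 and a non-panel type is recorded with HPV 16 only. A woman with the same non-panel type alone is recorded as carrying it. The chance of detection therefore falls as panel infection rises, and panel infection is what is expected to differ between the groups and to change with vaccination.

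Two uses are exposed:

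- A between-group comparison of a non-panel type is pulled down in the group with more panel infection.
- In a comparison over time, a net fall in panel infection brings previously hidden non-panel types into view. This is the direction that type replacement would also take.

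The study is meant to guide regional prevention policy, so either result could be taken at face value.

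**Working it through.** **Is there a plan figure to reproduce?** None bears directly on this point. The nearest is the Power calculation section, which calls 1000 women per high-risk group and 2000 controls adequate for genotypes at 1%–1.5% in controls, with 2–3 fold higher prevalence reported in the high-risk groups. It states no alpha or power. With two-sided alpha 0.05 assumed, power for a 2-fold contrast is 60% at 1% and 77% at 1.5%; for a 3-fold contrast it is 96% and 99.5%. The adequacy claim can be neither confirmed nor refuted from this, and the present point does not rest on it.

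**Which results are touched?**

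- Overall HPV prevalence comes from the ELSI PCR, which precedes typing, so it is unaffected.
- The panel list in HPV genotyping contains 16, 18, 31, 51, 52 and 53, so every type named in the Power calculation section is tested in each genotyped sample. These, like the other panel types, are unaffected.
- Only types outside the 28 are affected.

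**Model.** Let p be the true prevalence of a non-panel type, and m the share of its carriers who also have an assignable panel type.

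- Recorded prevalence = p × (1 − m).
- Recorded ratio = true ratio × (1 − m_high) / (1 − m_control).
- Under independence, m equals q, the prevalence of any panel type in that group.

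The document does not give q, so the values below are assumptions that show a range.

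| q control | q high-risk | factor | true ratio 2.0 appears as |
|---|---|---|---|
| 10% | 20% | 0.80/0.90 = 0.89 | 1.78 |
| 15% | 30% | 0.70/0.85 = 0.82 | 1.65 |
| 20% | 50% | 0.50/0.80 = 0.63 | 1.25 |

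Example with 15% versus 30%: a non-panel type truly at 1% versus 2% is recorded as 1% × 0.85 = 0.85% versus 2% × 0.70 = 1.40%. With 2000 and 1000 women and two-sided alpha 0.05 (assumed), power falls from 60% to 30%.

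**Change over time.** Let the prevalence of vaccine types fall from v to v1, with nothing else changing. Under independence the relative rise in recorded non-panel prevalence is (1 − v1)/(1 − v) − 1. For clustering, v is replaced by the vaccine-type share among non-panel carriers implied by a co-infection odds ratio of 3 or 5. All inputs are assumptions.

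| v to v1 | independence | odds ratio 3 | odds ratio 5 |
|---|---|---|---|
| 3% to 0.5% | 0.995/0.97 − 1 = 2.6% | 7.7% | 12.6% |
| 5% to 1% | 0.99/0.95 − 1 = 4.2% | 12.4% | 20.2% |
| 10% to 1% | 0.99/0.90 − 1 = 10% | 29.4% | 48.1% |

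**The case against.** **It belongs in the analysis plan.** The sequential typing is openly described, the remedy is an analysis rule, and a condensed article may leave such rules to a document not shown. The Cross-sectional study section says that type-specific prevalence will be estimated by group; it does not say that RFLP-identified types will be tested between groups. This limits the severity. It does not remove the point: the laboratory rule that creates the bias is fixed here, and the group and time analyses promised here would carry it if followed as written.

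**Its reach is small.** This stands. A reader might infer that HPV prevalence or type-specific prevalence in general is biased. The document does not support that, because overall prevalence and all 28 panel types escape the rule. The variant and escape-mutant objectives concern HPV 16 and 18 only.

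**A large single figure would be unsupported.** This also stands. A reader might take 15% versus 50% any-panel prevalence and read off a 41% deficit (1 − 0.50/0.85). Neither percentage is in the document. The 2–3 fold excess in the Power calculation section concerns individual types at low prevalence, not infection with any panel type. Only a range can be shown.

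**The replacement artefact may be lost in the noise.** Largely correct.

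- Suppose true non-panel prevalence is 6% and any-panel prevalence falls from 20% to 15% (all assumed). Recorded prevalence moves from 6% × 0.80 = 4.8% to 6% × 0.85 = 5.1%. With 2000 women at each time, treated as independent samples, the standard error is √(0.048 × 0.952/2000 + 0.051 × 0.949/2000), about 0.7 points. The shift is under half of that.
- Girls vaccinated at 12 from September 2008 are about 20 at most by December 2015, so the campaign cohorts do not enter the groups aged 26 or over.
- A reader might infer that each woman who clears a vaccine type adds to a false replacement signal. She does so only if no other panel type remains, and newly acquired panel types hide non-panel types in other women. Only a net fall in panel infection produces a trend.

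**Conclusion.** The point holds for types outside the 28-type panel and no further. Their recorded prevalence is too low in every group, and lowest relative to the truth where panel infection is most common. This direction follows from the testing rule, provided that the share of non-panel carriers who also have a panel type rises with panel infection, as it does under independence.

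The size rests on assumed any-panel prevalences: the true ratio is multiplied by 0.89 to 0.63 over the range shown. The spurious rise over time is modest, about 3–10% relative under independence for the assumed falls in vaccine types, and about 8–48% if co-infection odds ratios are 3 to 5. The document does not support calling any future replacement finding an artefact. It supports only that non-panel types, as tested, cannot carry such a claim on their own.

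The change should be made before analysis; the named between-group targets are not endangered.

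**What to change.** 1. In the Cross-sectional study section and for secondary objective (c), limit comparative claims on specific types, between groups or over time, to the 28 types tested in every genotyped sample.
2. Report RFLP-identified types descriptively, labelled as a non-panel type with no assignable panel type present, and state that denominator.
3. Reword the RFLP sentence in Baseline evaluation and follow-up to match the trigger in HPV X, including the unassignable-pattern case.

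The cost is a few sentences and no laboratory work. The real downside is scientific: no comparative or replacement claim can be made for types outside the panel, so objective (c) becomes narrower.
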